### Inclusion Criteria

(1) Age ≥ 18 years old;

(2) Acute decompensated heart failure was defined according to the “2021 ESC Guidelines for the diagnosis and treatment of acute and chronic heart failure” (13). Combined with symptoms, signs and laboratory results, and meet all the following conditions:

(2.1) At least one symptom was worsened from baseline: (a) dyspnea (dyspnea after exercising, paroxysmal nocturnal dyspnea or orthopnea), (b) venous congestion of systemic circulation (edema of lower extremities, liver congestion, ascites), and (c) tissue hypo-perfusion (oliguria or anuria, cold clammy limbs, consciousness disorder, hyper-lacticacidemia, or metabolic acidosis);

(2.2) At least one of the following signs of heart failure: (a) pulmonary edema on exam or by chest X ray, (b) Increased b-type natriuretic peptide or N-terminal prohormone BNP, and (c) abnormal cardiac structure and/or function by cardiac ultrasound;

(3) The symptoms and signs are consistent with acute decompensated heart failure judged by the investigator;

(4) Patients who have New York Heart Association Cardiac Function class III or IV symptoms at admission;

(5) Clinical stability has been achieved for 24 h after optimizing treatment;

(6) Patient was independent with basic activities of daily living including the ability to ambulate independently (with or without the use of an assistive device) prior to admission.

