### Sample Size

According to the results of the previous study, the baseline SPPB sores was 6.0 ± 2.8 in CR group and 6.1 ± 2.6 in control group, the SPPB sores at 3 months was 8.3 ± 0.2 in CR group and 6.9 ± 0.2 in control group (14). To minimize both false positive and false negative errors, the type-I error rate (α) is set at 0.01 instead of 0.05 and the type-II error rate is set at 0.1 instead of 0.2. The sample size is calculated according to the following formula: *n* = 2σ^2^ × *f* (α,β)/(μ_1_-μ_2_)^2^ (19). The sample size of each group was estimated to be 44 per group. Taking approximate a 20% drop-off rate and a 7% missing rate into account, the final sample size was set to 60 per group. Therefore, a total of 120 subjects will be recruited in this study.

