### Outcomes

The outcomes will be assessed by independent researchers who have been trained before the study. The primary outcomes are the SPPB score and 6-month all-cause rehospitalization. The secondary outcomes include cardio-pulmonary function, activities of daily living (ADL), in-hospital mortality rate and 6-month all-cause mortality rate. Cardiac function indicators are as follow: 6-min walking test (6 MWT) before discharge, SV before discharge, EDFR, SVR, NYHA classification, biochemical markers of myocardial necrosis, N-terminal brain natriuretic peptide (NT-pro BNP), and left ventricular ejection fraction (LVEF). Pulmonary function indicators include 1 second rate of transfer/discharge (FEV1/FVC) and maximum ventilation volume per minute (MVV). In addition, we will evaluate the Short-Form 36-Item Health Survey (SF-36), psychological assessment, nutritional assessment and cardio-cerebrovascular events (Table 2).

**Table 2 T2:** The follow-up schedule.

	**Baseline**	**1 month**	**3 months**	**6 months**
Smoking	X			
Sports	X			
Participate in phase II cardiac rehabilitation				
Psychological assessment	X		X	X
Nutritional assessment	X	X		X
Rehospitalization				
Cardio-cerebrovascular events				
36-item short-form (SF-36)	X	X	X	

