### Data Analysis

Statistical analysis will be conducted using SPSS 25.0 (IBM, Chicago, IL, USA) statistical software. *P* < 0.05 (two-sided) was considered to be statistically significant. Normally distributed continuous variables were presented as mean ± SD and evaluated with paired or unpaired Student's *t* test. Non-normally distributed continuous variables were expressed as median with interquartile range (IQR) and determined by Wilcoxon signed-rank test or Mann-Whitney U test. Categorical variables were recorded as frequency and percentage (*N*, %) and performed by χ^2^ test or Fisher's exact test as appropriate.

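### NYHA class is an ordered outcome, but on a plain reading the analysis rules send it to a chi-square or Fisher test that ignores the order (minor; power loss depends on assumptions)

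*Protocol article*

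**What the plan says.** The Outcomes section names the cardiac-function indicators, a group within the secondary outcomes, and NYHA class is among them: "EDFR, SVR, NYHA classification, biochemical markers of myocardial necrosis".

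The Data Analysis section gives general rules by type of variable and names no outcome:

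- Normally distributed continuous variables: paired or unpaired t test.
- Skewed continuous variables: "Non-normally distributed continuous variables were expressed as median with interquartile range (IQR) and determined by Wilcoxon signed-rank test or Mann-Whitney U test".
- Categorical variables: "Categorical variables were recorded as frequency and percentage (*N*, %) and performed by χ^2^ test or Fisher's exact test as appropriate".

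The significance threshold there is P "< 0.05 (two-sided) was considered to be statistically significant".

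Two other places bear on which classes will be seen. The Inclusion Criteria require "Patients who have New York Heart Association Cardiac Function class III or IV symptoms at admission". Table 1 links training levels to NYHA class: III–IV at Levels 1 and 2, III at Level 3, II–III at Levels 4 to 7. Class I does not appear in it.

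**The concern.** NYHA classes run from better to worse, and Table 1 uses them that way. The plan's rank tests are written for continuous variables only, so the one rule that fits a class variable is the categorical one. A chi-square or Fisher test on the table of class by arm gives the same P value if the class labels are shuffled. It asks whether the two distributions differ in any way, whereas the trial's hypothesis is directional: cardiac rehabilitation should improve function.

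Two things are at stake for this outcome. A general move towards better classes may be missed more often than the same data require. And a significant result need not mean improvement, because a change in spread alone can produce it.

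**Working it through.** **Plan's own figure.** There is none to reproduce. The article states no class distribution, expected shift, number of classes analysed or power for NYHA.

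**Inputs from the documents.** Arm sizes of 44 (evaluable) and 60 (randomised) from Sample Size; two-sided 0.05 from Data Analysis. Sample Size uses a different level ("the type-I error rate (α) is set at 0.01 instead of 0.05"), but 0.05 is the threshold stated for the analysis, so it is used here.

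**Assumed inputs.** Control-arm class distributions, and a common odds ratio (OR) of 1 to 4 in favour of the better classes.

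**Step 1: what the test responds to.** Two invented tables with 60 per arm, classes II/III/IV.

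*Spread only.* Control 12/36/12, CR 21/18/21. Expected counts per arm are 16.5/27/16.5. Chi-square = 4 × 4.5²/16.5 + 2 × 9²/27 = 4.91 + 6.00 = 10.91 on 2 df, P = 0.004. The Mann-Whitney P is 1.0, because neither arm is better overall.

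*Consistent shift.* Control 18/30/12, CR 28/25/7. Expected counts are 23/27.5/9.5. Chi-square = 2 × (5²/23 + 2.5²/27.5 + 2.5²/9.5) = 3.94 on 2 df, P = 0.14. For Mann-Whitney, of 60 × 60 = 3,600 pairs the CR patient is better in 28×42 + 25×12 = 1,476 and worse in 25×18 + 7×48 = 786. U minus its mean is (1,476 − 786)/2 = 345. The tie-corrected variance is (3,600/12) × [121 − 270,450/(120×119)] = 30,618, SD 175.0, so z = 1.97 and P = 0.049.

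**Step 2: power under a proportional shift.** For cumulative control probability c, the CR arm has odds OR × c/(1 − c). With control 30/50/20% and OR 2, the cumulative odds 0.429 and 4 become 0.857 and 8. The CR arm is then 46/43/11%. Pearson chi-square and tie-corrected Mann-Whitney were compared over 20,000 simulated trials per scenario.

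| Scenario, 60 per arm, OR 2 | Chi-square | Mann-Whitney | Difference |
|---|---|---|---|
| 3 classes, control 30/50/20% | 40.3% | 50.7% | about 10 points |
| 4 classes, control 10/40/40/10% | 35.9% | 52.6% | about 17 points |
| 2 classes, control 50/50% | 46.5% | 46.4% | about 0 |

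Mann-Whitney gain in points, over the assumed distributions and both arm sizes:

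| OR | 3 classes | 4 classes |
|---|---|---|
| 1.5 | 4–6 | 6–9 |
| 2 | 9–11 | 14–17 |
| 2.5 | 10–12 | 16–18 |
| 3 | 7–11 | 11–19 |
| 4 | 3–8 | 4–14 |

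At OR 1 both tests reject about 5% of the time. The exception is Pearson with nearly empty outer classes (2/48/45/5%), where it rejects about 3%; part of its loss there is conservatism. Fisher's test, which sparse tables would call for, was not simulated.

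**Step 3: shifts that are not consistent across classes.** The advantage can reverse. With three classes, control 30/50/20% and CR 50/30/20% (patients move from III to II, class IV unchanged), power at 60 per arm is 59.6% for chi-square and 37.5% for Mann-Whitney. With four classes, control 10/40/40/10% and CR 10/60/20/10%, it is 56.0% and 38.6%.

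**The case against.** The strongest reply has four parts.

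1. *The assignment is an inference.* Data Analysis never names NYHA, its categorical rule ends with a general qualifier, and matching each secondary indicator to a test is commonly left to an analysis plan, which is not shown. This stands as a limit on certainty. It does not remove the point, because the rules as written tie rank tests to continuous variables and leave only one that fits a class.

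2. *The size is not fixed by the documents.* A reader might infer from the four-class scenarios that the plan loses a flat 10 to 19 points of power. The documents do not support that. Everyone enters in class III or IV, training lasts 5 days, and Table 1 uses only classes II to IV. That points to two or three occupied classes, at least soon after the intervention, and so to the lower part of the range. This stands.

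3. *Direction would be visible.* Frequencies and percentages are to be reported, so a reader could see whether a significant result reflects improvement or spread. This stands in part: the table shows direction, but the P value still does not test it.

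4. *The consequence is small.* NYHA is one of several cardiac-function indicators under a secondary heading. It drives neither primary outcome nor the sample size, and no power is claimed for it. This stands and sets the priority.

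**Conclusion.** The point holds as a minor one. The written rules have no place for ordered categories, and the one that fits NYHA class ignores its order and does not target improvement.

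For a proportional-odds shift with OR 1.5 to 3, 44 to 60 per arm and two-sided 0.05, the cost is about 4 to 12 points of power with three occupied classes (II to IV, as in Table 1), about 6 to 19 with four, and about zero with two. All of these rest on assumed distributions and odds ratios, and the sign can reverse when the effect is not a consistent shift.

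A reader might also infer that the chi-square result would be invalid. It would not be: its false-positive rate is at or below the nominal level in the scenarios run, and the issue is efficiency and relevance to the question. Nor do the documents show a deliberate choice of chi-square for NYHA.

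**What to change.** In Data Analysis, add a sentence along these lines: ordered categorical outcomes such as NYHA class will be compared between arms by the Mann-Whitney U test, with a common odds ratio and 95% CI from a proportional-odds model; chi-square or Fisher's exact test is kept for binary and unordered variables.

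The cost is that sentence. Mann-Whitney is already in the plan, and no new data or patients are needed. There are two downsides. Power is lost, as in Step 3, if the effect is confined to one step of the scale or runs in both directions. And the odds ratio relies on the proportional-odds assumption, which the rank test itself does not need. Settling this before the data are analysed also avoids choosing between the two tests afterwards.

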## Discussion

This is a study protocol for a single-center, randomized controlled, single-blind clinical trial to evaluate the efficacy and safety of phase I CR in patients hospitalized in CICU with ADHF. The results of this study will provide reliable evidence for tailored and progressive CR intervention in patients with ADHF.

CR is one of the treatment strategies for HF, which services as one way to reduce the financial burden of HF treatment (24). A recent trial showed CR could improve physical function in patients with ADHF, especially those in NYHA Class II group (14). CICU is usually needed for the patients with ADHF presented with signs of respiratory distress, hypoperfusion, and hemodynamic instability. These patients are at high risk for unexpected in-hospital mortality and re-hospitalization (25). Whether personalized, tailored, and progressive CR intervention is associated with improved QOL and outcomes in patients in CICU with ADHF has not yet been clarified. Thus, evidence on the efficacy and safety of CR intervention is needed in individuals enter the CICU with ADHF.

Tailoring exercise prescription based on the characteristics of patients is necessary for the development of CR in ADHF. Improved SPPB score was related to better prognosis in patients with HF (26). The PEARL study and the REHAB-HF trial showed CR could improve the SPPB score among elderly patients with ADHF (14, 27). However, re-hospitalization rate was not included as a study endpoint in PEARL study. In REHAB-HF trial, reduced re-hospitalization rate was not observed in CR group during the follow-up period. In addition, the majority of CR interventions were conducted in the outpatient setting in REHAB-HF trial. We hypothesize early phase I CR training will increase the SPPB score and reduce the re-hospitalization rate. Additionally, our personalized, tailored and progressive CR program include comprehensive physical fitness interventions. The physical fitness interventions include strength, flexibility, coordination, and balance training. The psychological interventions will be performed by specialized psychological intervention therapists. To achieve the outcomes, strict follow-up procedure will be conducted for 6 months. These measures could promote individualized CR intervention in patients with ADHF.

In conclusion, we aim to explore the efficacy and safety of CR in patients with ADHF hospitalized in CICU through this clinical trial. The research results are expected to help provide further evidence for clinical application and guidelines. Subsequent studies will need to demonstrate sufficient efficacy and safety of CR in patients with ADHF.

## Ethics Statement

The studies involving human participants were reviewed and approved by the Ethics Committee of Xiamen Cardiovascular Hospital of Xiamen University. The patients/participants provided their written informed consent to participate in this study.

## Author Disclaimer

The content is solely the responsibility of the authors and does not necessarily reflect the views of the organizations listed above.
